## Study population

### Subject Inclusion Criteria

- Must be currently receiving combination antiretroviral therapy (cART) or co-trimoxozole prophylaxis from one of the eligible study clinics:
  - Is currently in care at study baseline, defined as having ≥1 medical care visit to receive medications (cART or prophylaxis) during the six months preceeding initiation of study enrollment, OR
  - Initiates pre-ART or ART care for the first time at a study clinic during the six month study recruitment period, OR
  - Transfers from a clinic outside the study area and receives pre-ART or ART care for the first time from a study clinic during the six month recruitment period
- Participants become eligible for study inclusion on the 4th day following a missed clinic appointment, provided the patient has not transferred care to another clinic prior to the 4th day, moved outside the study area or died. Participants who miss a study visit by >3 days but return to clinic before recruitment takes place are still eligible for study enrollment.
- Must currently reside on Mfangano, Remba or Ringiti Island.
- Must be conversant with one of the commonly spoken languages within the study area (i.e. DhoLuo, Swahili or English; prior experience indicates that this represents >99% of the adult population).
- Must be ≥18 years of age as of the date of study eligibility.

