The accessible population for this study includes all patients in HIV care and treatment, regardless of ART status, at the Sena (excluding patients residing in the East sub-location), Yokia, Ugina, Nyakweri, Wakula, Soklo, Remba and Ringiti Health Centers. Excluding patients residing in the Mfangano East sublocation from the total in Table 1, results in approximately 1500 current adult patients in these clinics. Extrapolating data from the MIHNIS study would suggest that 65% of these patients would become eligible for the Kanyakla Study during study enrollment. However, based on more recent observations at the included study clinics, we expect that only about half of the expected number of patients will become eligible. If we assume that 32% will become eligible that 75% of those who are elibigle will be willing to participate in the study, we will have an accessible population of 365 or approximately 180 per arm. Thus, because the accessible population is larger than the estimated sample size, we will extend our sample size to include up to 180 participants in each arm to allow for errors in these sample size calculations.

*Sampling Procedure*

Sampling will take place at included study clinics on a bi-weekly basis. Study staff will use information from the clinic daily activity log, master facility log and defaulter logs to identify all eligible patients who have missedclinic visits by >3 days. All eligible patients will be sampled for the study.

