## Procedures

### Study Design Overview

This is an individual randomized control trial evaluating the impact of the social network-based microclinic intervention on engagement and retention in HIV care over twelve months of follow up among individuals who have missed a clinic appointment by >3 days.

Study enrollment will occur over a six-month period. Upon meeting eligibility criteria, study staff will trace participants in the community to enroll them in the study. Eligibility will be determined using an Eligibility Determination Form, adapted from the FACES Loss to Follow-Up form (Appendix A). Study staff will counsel all eligible participants to return to clinic. After this counseling session, study staff will explain the purpose of the study and the nature of the intervention. After answering all participant questions, interested participants will be consented to participate (Section IX.c and Appendix H). Following study enrollment, participants will be randomized to intervention or control arm. Those randomized to intervention will be invited to recruit their social network members to form a microclinic. Study staff will provide confidential assistance to help discreetly identify and recruit family, friends, and neighbors to join the program based on previous protocols developed during the Mfangano Health Net Microclinic Pilot Program. Participants randomized to the control arm will be invited to form a microclinic group after the conclusion of the study.

Baseline measurements for index participants (i.e. participants who are eligible based on missed clinic visit) will be taken at study enrollment, with study staff administering a survey to collect data on baseline participant characteristics (Appendix C). Reasons for initial disengagement from care will also be recorded.

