### Measurements

The predictor of interest is the baseline treatment assignment, as determined by randomization. All analysis will be conducted using an intention-to-treat analysis.

Covariates of interest will be collected through participant surveys at baseline and study closure, as well as routine clinic data collected at the participant’s original clinic and any other clinics from which he or she receives HIV care during the course of the study. Baseline surveys (Appendix C) will collect data related to the following:

1. Demographic characteristics
2. Contact and locator information
3. HIV-related stigma[23](#_ENREF_23)
4. HIV status disclosure
5. Social support
6. Clinic data (date first HIV positive, date of enrollment)
7. Reason for missed clinic appointment, including name of other facilities where care was received

At the end-of-study survey (Appendix G), additional data will be collected related to possible adverse events that may or may not be related to the intervention. In addition to specific questions in the survey, an open-ended question will be used to assess other adverse experiences related to issues such as stigma, unintended disclosure or poor treatment by health center staff. Participants will be asked whether they attribute any or all of these experiences to participation in the study. Additionally, participants in the intervention arm will specifically be asked about adverse experiences related to group status disclosure, again using both a checklist and an open-ended question. At the end-of-study survey, patients will be asked if they are currently in care and, if so, which clinic. Reasons for transfer or disengagement from the original clinic will be assessed. For patients who were lost-to-follow-up (missed a clinic visit by ≥90 days and did not return to clinic) or who transferred out from their original clinic, a patient tracing survey will also be conducted. (Appendix F) See description of clinic data capture below regarding determination of patient’s visit history and transfer status.

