| A11a. Why was tracking not attempted? | |  Contact information illegible   **END**   Contact information missing   **END**   Chart missing  **END**   Patient permanently moved outside study area  **END** | | | | | | | | | | |  Location listed too general to make tracking possible   **END**   Chart reviewed and patient not lost to follow up  ** go to A11b**   Other, specify:   **END** | | | | →A11b. What is patient outcome? | | | |  Has recent visit – doesn’t  meet definition of lost-to-follow-up   Transferred to clinic within study area   Transferred to clinic outside study area   Dead  Date:- - | | | | | | | | | | | |
| A12. Source of locator information | | | |  Paper file Electronic database   No locator information in paper or electronic database  Other, specify:…………………………… | | | | | | | | | | | | | | | | | | | | | | | | | | | | |
| **SECTION B: TRACKER COMMUNICATES WITH PATIENT** | | | | | | | | | | | | | | | | | | | | | | | | | | | | | | | | |
| B1. Interview type. *Mark all that apply:* | | | | | | | | in-person phone | | | | | | | | B2. Interview date. | | | | | | - - | | | | | | | | | | |
| DAY(*dd*) | | | MONTH (*mmm*) | | | | | YEAR (*yy*) | | |
| B3. Confirm identity of patient using as many identifiers as possible. *Mark all that apply:* | | | | | | | | | | | | | | | | | | | | | | | | | | | | | | | | |
|  Name  Age  Sex  Height  Location or residence  Occupation  Clinic number or medical papers | | | | | | | | | | | | | | | | | | | | | | | | | | | | | | | | |
| B4. Have you seen a doctor or nurse for the care or treatment of HIV within the last four weeks? | | | | | | | | | | | | | | | | | | | | | | | | | | | | | | | | |
| Yes | →B4a. Where?  *Mark all that apply.* | | | | |  Original clinic  **→ Question patient about missed visit**   Different clinic   Other, specify: | | | | | | | →B4b. Name of clinic or other: | | | →B4c.  When did you first make a visit to **any** new clinic? | | | | | | - - | | | | | | | | | | |
|  | | |
| DAY  *dd*) | MONTH (*mmm*) | | | | | | | | YEAR(*yy*) | |
|  | →B4d. Why are you going to [new clinic] instead of your previous one? *Answer both coded and descriptive responses* | | | | | Coded responses: *Mark all that apply* | | | | | | | | | | | | | | | | | | | | | | | | | | |

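### Appendix A screens charts with a lost-to-follow-up test that is not the entry criterion, so eligible patients who have already returned to clinic can be passed over without contact

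*Protocol*

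**What the plan says.** The Subject Inclusion Criteria set the entry point: "Participants become eligible for study inclusion on the 4th day following a missed clinic appointment". They then add: "Participants who miss a study visit by >3 days but return to clinic before recruitment takes place are still eligible for study enrollment". (In context, the study visit there is the missed clinic appointment.) The Sampling section says that every eligible patient identified from the clinic logs is sampled, every two weeks. The Study Design Overview makes Appendix A, adapted from a loss-to-follow-up form, the instrument that determines eligibility.

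In Appendix A, item A11 sends staff to Section B, C or D according to who was reached, or to A11a if tracking was not attempted. One A11a reason is "Chart reviewed and patient not lost to follow up", which leads to A11b. The A11b outcomes are a recent visit that is said not to "meet definition of lost-to-follow-up", a transfer within the study area, a transfer outside it, and death. The form does not define lost to follow-up. The definition in the protocol body, under Measurements, is "missed a clinic visit by ≥90 days and did not return to clinic".

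Elsewhere the same form treats returners differently. For a contacted patient seen recently at the original clinic, B4a instructs staff: "Question patient about missed visit". F1c makes a contacted patient in care at the original facility ineligible only where the missed visit was a clinic record error.

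**The concern.** Being lost to follow-up is not an entry criterion. A patient who missed by more than 3 days and came back before recruitment is eligible under the inclusion criteria and is plainly not lost to follow-up. At A11a/A11b that patient can be closed out from the chart alone. Whether an eligible returner is invited may then depend on whether staff read the chart first or meet the patient first.

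The entry rule defines the population for which the trial was planned. The 25% control event rate (36 of 145 pilot controls) is for people who missed by more than 3 days, with no condition on having stayed away. The 32% eligibility figure is about half of the pilot's 65%, which was counted the same way. If returners drop out at the chart stage, the enrolled group is narrower than the planned one and may differ between clinics in a way that the screening record does not explain.

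**Working it through.** **Two routes for one patient.** Take a patient who missed by 6 days, returned on day 7, and appears in the next two-weekly sampling.

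| Route | Items | Result |
|---|---|---|
| Contacted | A11, Section B (B4a), Section E, Section F | Questioned about the missed visit; eligible at F1 unless the miss was a record error; invited |
| Chart read first | A11, A11a, A11b | Recent visit recorded; no contact and no onward instruction |

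Sections B, C and D lead to Section E, and Section F follows it. A11b leads nowhere. Its other outcomes are transfer and death, so a recent visit sits among reasons to stop. The F1c reasons are grouped by patient contacted, informant interviewed, or neither located; there is no group for a chart-only decision. The likely origin is visible in the Lost to Follow-Up Tracing Form, which has nearly the same A11a/A11b pair. There, not being lost is a proper reason not to trace.

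**The plan's figures.** Inputs from Sampling: p0 = 0.25, p1 = 0.125, alpha 0.05 (two-sided assumed), power 80%, m = 2 participants per group, coefficient of variation k = 0.25.

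- Hayes-Bennett formula: c = 1 + (1.96 + 0.842)² × V / (p0 − p1)², where V = p0(1−p0)/m + p1(1−p1)/m + k²(p0² + p1²).
- V = 0.09375 + 0.05469 + 0.00488 = 0.15332. So c = 1 + 7.849 × 0.15332 / 0.015625 = 78.02 groups, or 156.03 participants per arm. Stated: 156.
- Attrition: 156 / 0.90 = 173.3, rounded up to 174. Stated: 175.
- Pool: 1,500 × 0.32 × 0.75 = 360. With half of 65% (0.325) it is 365.6. Stated: 365.

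All three reproduce within rounding.

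**Margin.** The number to be sampled is 2 × 175 = 350. The pool falls below it after a loss of 10/360 = 2.8% or 15/365 = 4.1%. The evaluable requirement is lower, 2 × 156 = 312. At the pilot's 98.6% ascertainment, 312 / 0.986 = 317 enrolled would suffice, which tolerates a loss of 43/360 = 12%.

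**Illustration only.** The share lost at A11b is not in the documents, so the shares below are assumed. Pool 360, 10% attrition, planned event rates, power = Φ(√[(c − 1)(p0 − p1)²/V] − 1.96), with c = evaluable per arm / 2.

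| Assumed share lost | Enrolled | Power |
|---|---|---|
| 0% | 360 | 0.815 |
| 10% | 324 | 0.772 |
| 20% | 288 | 0.722 |
| 30% | 252 | 0.664 |

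These values hold the event rates fixed. If those remaining had a higher control rate and the same halving of risk, the loss could be offset. Ignoring clustering, 288 patients give power 0.734 at 0.25 v 0.125 and 0.828 at 0.30 v 0.15.

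**The case against.** The strongest reply is that the form never says returners are excluded. Of the seven A11a reasons, six are marked as an end point, and the one quoted is the exception. A11b carries neither an end mark nor the word ineligible. No branch of the form points explicitly to Section F, so the lack of that pointer at A11b proves little by itself. The eligibility decision is made in Section F, where F1c agrees with the inclusion criteria. The recruitment section has staff attempt to locate those sampled, so the not-attempted path should be uncommon. All of this stands. A reader might infer that Appendix A excludes returners outright; the text supports only that it allows them to be passed over.

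A reader might also infer that the trial would enrol a smaller, longer-absent group and be underpowered. The documents do not support that. They give no rate of return before tracing and no data showing that returners have a milder course. The pool inputs are cautious: 75% willing against 89% who joined in the pilot (1,500 × 0.32 × 0.89 = 427). The attrition allowance is described as conservative, and a higher event rate could compensate for fewer patients.

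Nor is bias between arms a fair inference. The form is completed before consent and randomisation, and randomisation is stratified by clinic.

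What the reply does not remove is the wrong test at A11a/A11b and the different handling of the same patient within one form.

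**Conclusion.** The point holds as an inconsistency in the eligibility instrument that should be corrected. A11a/A11b apply a lost-to-follow-up test where the entry criterion is an appointment missed by more than 3 days, and they leave an eligible returner with no route to contact. The consequence is possible rather than certain: an enrolled population narrower than the one behind the planning assumptions, and dependent on how staff or clinics use the form. Two-weekly sampling and the standard follow-up visit by clinic staff make early returns plausible but do not quantify them. No sample-size figure is wrong, a net loss of power is not established, and the randomised comparison remains valid for those enrolled. The conclusion assumes that staff may read A11b, which has no onward step, as the end of the process.

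**What to change.** In Appendix A:

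- Keep the A11a route to A11b, with its transfer and death outcomes. This is the form's only chart-review route to those outcomes, and patients who did miss by more than 3 days still need it. The A11a option should therefore not itself be reworded to say that no such miss occurred.
- Remove the lost-to-follow-up wording from both items and refer instead to the >3-day missed-appointment criterion.
- Split the recent-visit outcome in A11b: (a) no appointment missed by more than 3 days, end, not eligible; (b) missed by more than 3 days and since returned, go to contact (Section B) and then Section F.

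If a population still absent at recruitment is what the sponsor intends, the inclusion criterion and the event-rate and eligible-pool assumptions under Sampling must be reconciled with the form instead.

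The cost is rewording two form items before recruitment. Staff must also contact patients who are already back in care, which the inclusion criteria already imply.

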Participants randomized to control will be told that they are eligible to form microclinic groups following the conclusion of the study. They will be counseled on the importance of social support in their HIV care and will be clearly advised that assignment to the control group should not prevent them from discussing their HIV care with those close to them. As is true for all participants who are recruited for the study, they will be advised to return to the clinic. Beyond the counseling to return to clinical HIV care provided by study staff, standard of care for patients who have missed a clinic visit is to receive a follow-up visit from clinic staff to facilitate return to care. Study staff will collaborate with clinic staff to ensure that all study participants receive a visit from study staff and clinic staff to encourage return to care.

Orientation meetings will be conducted on a bi-monthly (every other month) basis with all newly formed microclinic groups. This meeting will include the following:

- The microclinic intervention will be explained to all prospective group members and a brief orientation to the curriculum will be provided.
- Study enrollment of social network members who were not originally enrolled through eligibility determination at the clinic. These ‘social network members’ will be consented for study participation (See Appendix I, Consent document for Microclinic Group Members), but will not be included in primary study analysis. Data from these participants will only be used for purposes of understanding the characteristics of those who were selected for microclinic participation and how their characteristics impact outcomes among index participants. For ‘social network’ participants, study participation will involve survey administration and data collection on participant HIV and clinic status in order to understand microclinic group composition. Study enrollment is voluntary and refusal will not prevent social network group members from participating in the microclinic group meetings. Aside from reasons for refusal, no data will be collected for social network participants refusing study enrollment.
- All group members will undergo individual confidential HIV testing (group members who are known to be HIV-infected will attend a counseling session but will not be tested).

[figure not shown]

**Figure 1.** Participant flow diagram

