The microclinic intervention includes participation by members of the index patient’s social network. This may include other index patients, or community members who are HIV-infected, HIV-uninfected or of unknown HIV status. These non-index microclinic members, referred to as ‘social network’ participants, will be invited to join the study in addition to participation in a microclinic group. Microclinic participant is not contingent on study participation, however data will only be collected for microclinic group members who also consent to study participation.(Appendix I) For social network participants, study participation involves completion of a baseline survey to collect information on sociodemographic characteristics, HIV-related stigma, previous HIV testing, HIV status, and enrollment and engagement in HIV care (if HIV-infected).(Appendix D) For each microclinic group, a Microclinic Group Member Information form will also be completed to describe the nature of the realtionships between group members.(Appendix E) Only group members who consented to study participation will be included. At the time of group enrollment, all prospective social network study participants will be invited to enroll in the study. Following study enrollment, these surveys to collect information on sociodemographic characteristics and HIV-related stigma will be administered by trained study staff. Data on previous HIV testing, HIV status and enrollment and engagement in HIV care will be collected by a trained Voluntary Counseling and Testing (VCT) counselor as part of a baseline HIV counseling and testing session. Refusal to participate in the study will not preclude social network group members from participating in the microclinic group, but no study data will be collected on these participants.

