| E1. In the last 6 months, I received assistance/support from any friends or family in attending my HIV clinic appointments |  |  |  | |  |  |
| E1b. Please check all types of support received: |  Encouragement   Reminders   Financial assistance   Transportation (non-financial) | | |  Help with duties at home (i.e. childcare, chores)   Help with duties at work   Accompanyment (i.e. someone goes with me to my appointments) | | |
| E2. In the last 6 months, I received assistance/support from any friends or family in taking my HIV medications |  |  |  | |  |  |
| E2b. Please check all types of support received: |  Encouragement   Reminders   Gives me food to take with medications   Advice about side effects | | |  Observation (someone watches me take my medications)   Accompanyment (someone takes their medications with me at the same time) | | |

| Kanyakla Study  Date of Interview: //  Day Month Year | | | | | | | | | Participant ID:  Interviewer Initials: | | | | | |
| --- | --- | --- | --- | --- | --- | --- | --- | --- | --- | --- | --- | --- | --- | --- |
| ***TO BE COMPLETED BY VCT COUNSELOR*** | | | | | | | | | | | | | | |
| **SECTION A. HIV TEST** | | | | | | | | | | | | | | |
| A1. | Age: |  | A2. | Gender  Male   Female | | | | | | | | | |  |
| A3. | Have you been tested for HIV before? | | 0  No  Skip to A8.  1  Yes  A3a. and A3b. | | | | A3a. | What was the result?   Negative   Positive (A3b.) | | | | A3b. | What date did you find out you were HIV positive?  : //  Day Month Year | |
| A4. | Have you ever enrolled in HIV care? | | 0  No  reasons why not enrolled, then skip to **section B**  1  Yes | | | | | | | Reasons why not enrolled: | | | | |
| A5. | Which clinic? | | |  Sena   Yokla   Nyakweri   Wakula   Ugina   Soklo   Takawiri   Ringiti   Remba   Other - specify ______________ | | | | | | A6. | Enrollment date  //  Day Month Year | | | |
| A7. | On ART?   No   Yes (record date of initiation)  //  Day Month Year | | | |
| A8. | What is the result of the test today? | | | |  Negative   Positive   Indeterminant | | | | | | | | | |
| **SECTION B. DISCLOSURE** | | | | | | | | | | | | | | |
| B1. | Not counting healthcare workers, have you disclosed your HIV status to anyone? | | | | | 0  No ** Skip to SECTION C.**  1  Yes | | | | | | | | |

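### As printed, the network-member HIV form takes members with an earlier negative test past the item for today's result, although the protocol says they are tested that day

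*Protocol*

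**What the plan says.** Protocol, Subject Recruitment and Enrollment, sets the testing rule for the orientation meeting: "All group members will undergo individual confidential HIV testing". It makes one exception: "group members who are known to be HIV-infected will attend a counseling session but will not be tested".

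Protocol, Study Design Overview, says how network members' data are obtained: "Data on previous HIV testing, HIV status and enrollment and engagement in HIV care will be collected by a trained" counselor at the baseline counseling and testing session. The recruitment section gives the purpose: to describe who was chosen for the groups and how their characteristics bear on index participants' outcomes. It adds that network members "will not be included in primary study analysis".

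The form for this session is in Appendix D (Microclinic Group Member Survey Form), Section A, items A3 to A8:

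- **A3**, tested before: No goes to A8; Yes goes to A3a and A3b.
- **A3a**, "What was the result": Positive leads to A3b, the date the member learned of the infection. No route is printed for Negative.
- **A4**, "Have you ever enrolled in HIV care": No carries the instruction "reasons why not enrolled, then skip to section B"; Yes continues to A5 to A7.
- **A8**, "What is the result of the test today": Negative, Positive or Indeterminant.

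**The concern.** The testing rule and the form's routing should pick out the same people: whoever is tested that day should reach the item for that day's result. As printed they do not. Someone with an earlier negative test has had no reason to enroll in HIV care, so answers No at A4 and leaves Section A before A8.

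What is at stake is the baseline HIV status of network members. Among the forms shown, A8 is the only place for the same-day result; the group information form (Appendix E) records name, ID, gender, age and relationships, but not HIV status. Without A8, an earlier negative who is infected now cannot be told apart from one who is still negative. The protocol wants these data in order to relate group make-up to index outcomes.

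**Working it through.** No sample-size or error-rate figure is involved and the plan states no figure of its own to reproduce. The check traces the printed routing for each type of respondent and sets it against the testing rule.

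**Inputs.** Routing of A3 to A8 from Appendix D, Section A. Testing rule from Subject Recruitment and Enrollment.

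| Type of member | Printed route | Tested that day? | Reaches A8? | Consequence |
| --- | --- | --- | --- | --- |
| Never tested | A3 No, A8 | Yes | Yes | Result recorded |
| Earlier negative, never in care | A3 Yes, A3a Negative, A4 No, Section B | Yes | No | Result has no entry |
| Earlier positive, never in care | A3 Yes, A3a and A3b, A4 No, Section B | No | No | Nothing lost |
| Earlier positive, enrolled in care | A3 Yes, A3a and A3b, A4 Yes, A5 to A7, A8 | No | Yes | No result to enter, and no option to say so |

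The first and third rows work. The second loses a result that exists; the fourth asks for one that does not.

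**Size of the loss.** Let T be the number of members tested that day, that is, those not known to be positive, and q the fraction of them tested before. Assume earlier negatives have never enrolled in HIV care. Those bypassing A8 number q × T, so the share of same-day results with no entry is (q × T) / T = q. The protocol does not give q, so it is an assumption:

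- q = 0.2: 20%
- q = 0.5: 50%
- q = 0.7: 70%
- q = 0.9: 90%

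**Missing is not the same as wrong.** An earlier negative who is still negative is described correctly by A3a, only without a date or confirmation. The form is wrong only for earlier negatives who test positive that day. If a fraction p of earlier negatives do so, the wrongly described share of tested members is q × p. The protocol gives neither factor, and the 20% to 90% above must not be read as a misclassification rate.

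**After the correction.** With A3a Negative routed to A8, every tested member reaches A8 and the share without an entry falls from q to 0.

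**The case against.** The strongest defense is that asking why someone did not enroll in HIV care makes sense only for a person known to be infected. A4 to A7 were therefore probably meant for earlier positives, and a trained counselor completing the form might see that. On that reading the jump from A4 to Section B agrees with the testing rule, and the fault is the missing branch at A3a. This stands as to where the fault lies. It does not remove the fault, because the restriction is not printed. The protocol has survey data captured on tablets (Data Verification and Security; Data Collection and Storage). The programmed logic is not shown, but if it follows the printed skips, A8 would not be offered to these members.

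A second objection is that visit histories and clinical data, including the date of the first HIV test, are collected for participants in care at study clinics. A new positive who enters care there could be identified later. That is true, but it does not cover those who do not link to care.

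Third, no trial conclusion depends on this item. Primary analyses use index participants only, and none of the five hypotheses uses network members' HIV status. This stands and limits the weight of the point.

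A reader might go further and infer that HIV status is lost for most people tested. The documents do not support that. A majority requires q above 0.5, which is nowhere established. Status is not wholly lost either: A3a keeps the earlier result, and only that day's result is missing. Nor does every previously tested member outside care lose something, since known positives in that group are not tested.

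**Conclusion.** The point holds as a routing error on a data form. Followed as printed, Appendix D leaves no entry for the same-day result of members with an earlier negative test, whom the protocol says are tested. It also sends known positives in care to a result item that does not apply to them. The share of tested members affected equals the previously tested fraction among those not known to be positive. It is unknown, and 20% to 90% is only an illustration over assumed fractions of 0.2 to 0.9. The calculation assumes that earlier negatives have never enrolled in HIV care and that staff or tablets follow the printed skips.

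The damage is confined to the description of group composition and any analysis relating it to index outcomes. It would be too strong to conclude that those analyses would run on broadly misclassified HIV status. Only new positives among earlier negatives would be described wrongly, and the protocol gives no number for them. The primary analysis is unaffected. The correction is still worth making before the form is used, because a result not captured at the session may not be recoverable later.

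**What to change.** In Appendix D, Section A:

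1. Route A3a Negative directly to A8.
2. Limit A4 to A7 to members with an earlier positive result.
3. Keep the route from A4 No to Section B for those members. It agrees with the testing rule, and sending them to A8 would ask untested people for a result.
4. Add an option to A8 for members not tested because they are known to be HIV-infected, or send known positives in care from A7 straight to Section B.

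Check that the tablet version carries the same routing. The cost is a form revision and a change to the skip logic. No procedure is added, because the test is already planned, and Sections B and C stay as they are.
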